### Intervention

Participants in the intervention group will be given access to a 6-min educational video 5 days after discharge from the hospital. This will allow the participants to become settled at home or at a training centre to ensure their receptiveness to the intervention. The educational video will present dietary recommendations from the *Kostholdshåndboken* (English: *The Diet Handbook*) published by Helsedirektoratet [58]. The dietary guidelines recommend that malnourished older adults increase their energy and protein intake and provide examples of how older adults can adapt and integrate the recommendations into their preferences and daily mealtime routines [58]. As the participants in the intervention group will be required to access the educational video via their email or smartphone, the video will be made accessible individually through a link sent out by the first author. Through the video, the participants will be encouraged to watch the video several times, with, for example, their relatives or other health personnel. Since it will not be possible to personalise the intervention to each participant, the video information on food and nutrition is based on the following general principles:The information should be simple and correct, according to Contento and Koch [59]; this means keeping the words simple, since the field of nutrition can be full of technical jargon.The information is presented using the active voice rather than the passive voice, since this makes the text more personal [59].The length of sentences varies but is generally kept short [59]. The text of the education manual has undergone several ‘translations’ and revisions to make it easier for people with different assumptions and needs for information to understand. To prevent confusion among patients and strengthen the study’s criterion validity, we collaborated with a nutritionist who provided daily information to the user group to ensure we used precise words and expressions. Furthermore, the face validity of the educational video was confirmed by two bed-ridden patients in the user group who read the script and gave oral and written feedback on its contents. The intervention patients in the feasibility study did not have problems understanding the content, and significant changes in nutritional intake were observed.

In making the video, we used visual effects and pictures of different products so that participants would be able to imagine other food options more easily. Product images were obtained following current legislation, and there are no conflicts of interest or collaboration between the producers of the product images and the study’s authors.

The control group will have no access to the video and will not receive other intervention dietary advice in relation to this study. The selected hospital performs nutritional screening of patients in connection with admission as a part of the standard procedure at the hospital but does not provide nutritional information brochures or similar information upon discharge. However, as a standard procedure at the selected hospital, malnourished patients can receive advice or follow-up from healthcare professionals such as nutritionists on request, regardless of the intervention. No concurrent treatment or intervention will take place during the trial.

To strengthen retention, the participants in the intervention group will get a text message each week for the first 3 weeks after discharge and be contacted by phone to reduce technical problems opening the link, etc.

At follow-up after 3 months, the participants in the intervention group will be asked if they have seen the video and if they can remember how many times they have seen it. At the end of the intervention period, the authors will meet to review that both participants in the intervention group have been given access to the intervention as planned and that the intervention has not been given to the control group. The education video will not be modified during the course of the study.

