### Sample size

We base our calculation of the sample size on the effect estimates of the primary outcome of the combined physical scale from the feasibility study, as estimates were not available in the literature [53]. Alpha was set at 0.05, and the beta was set at 0.20. The estimated effect size was calculated to be 7 points on a scale ranging from 0 to 100, and the standard deviation of the population outcome was 18. The patients will be distributed with 50% in the control and intervention groups. Using the sample size-means calculator [56], the necessary sample size was calculated to be 104 in each of the 2 groups. Based on the feasibility study [53], we estimated a drop-out rate of 32%. Therefore, we need to recruit 138 participants for each group.

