### Randomisation

Complete randomisation will be achieved using the free software program RANDOM.ORG [57]. The first author will use the program to allocate participants to the inclusion group or the control group randomly. The study will be blinded to the care providers and data collectors, including the external data collector who will perform the outcome assessors and the statistician (investigator). A code will be allocated to each patient and not revealed before the analysis has been completed. Once the analysis has been completed, the group to which participants had been allocated will be revealed. Due to the nature of this study, where the participants will be aware whether they will have access to the educational video, it is not possible to achieve blinding for the participants.

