#### Monitoring

The first author will continuously monitor the study in relation to registration. Specifically, (1) data will be exhaustively registered, (2) the number of potential participants who refuse to participate will be tracked, (3) participants who have viewed the education video will be contacted 1 week after they have received the video to check that they have been given access to it and (4) participants and their relatives will be contacted to ensure they have received information on how to contact the project management group in the event that they have questions or unwanted incidents occur.

Furthermore, a steering committee will be responsible for providing support for the study. Members of the steering committee will be from Nord University, leaders from the involved wards at the hospital and a user representative. The primary author will be the secretary for the steering group. The steering committee will meet at least monthly and receive reports of the study’s progress each week.

The first author will inform the steering committee if changes to the protocol occur, and any deviations from the protocol will be fully documented. Changes in the protocol will also be updated in the clinical trial registry. Since the research will be done at only one hospital and this is a low-risk intervention, a coordinating centre, project management group or data monitoring committee will not be needed.

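### Retention texts are planned for the intervention arm only, which risks allocation-dependent drop-out and mixes contact with the video effect

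*Protocol article*

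**What the plan says.** All references are to the protocol article.

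- **Intervention:** "To strengthen retention, the participants in the intervention group will get a text message each week for the first 3 weeks after discharge". The same sentence adds phone contact to reduce technical trouble with the link; the number of calls is not given. The control condition is described in the same section as no video and no study dietary advice, with no retention contact mentioned.
- **Monitoring:** "participants who have viewed the education video will be contacted 1 week after they have received the video", in order to check access. Only the intervention arm can receive this contact. A further item, not limited by arm, has participants and relatives contacted about how to reach the project group.
- **Randomisation:** "it is not possible to achieve blinding for the participants".
- **Primary outcome:** the RAND 36, scored from the participants' own answers.
- **Sample size:** a 7-point effect, SD 18, 104 evaluable and 138 recruited per group, and one overall drop-out figure of 32%, not split by arm.
- **Aim of the study:** to test the effectiveness of an educational video.
- **Data analysis:** intention-to-treat principles, and an attrition analysis by gender, age, education, marital status and home care.

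**The concern.** The protocol itself gives retention as the purpose of the texts. Retention means that the participant is still there to be measured 3 months after discharge, and the comparison needs that equally from both arms. A retention measure given to one arm can make the chance of being measured depend on allocation.

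Two things are at stake.

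1. **Unequal loss.** If those lost differ in quality of life from those retained, unequal loss shifts a comparison of completers. The intention-to-treat principle keeps each participant in the assigned arm, but it does not supply an outcome that was never observed. The attrition analysis describes who is lost and does not correct for it.
2. **Contact mixed with content.** The arms differ by the video, the texts and the phone contact together. Participants know their arm and rate their own health, so blinding the data collector does not protect the primary outcome from a response to being contacted.

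**Working it through.** **Step 1. Reproduce the planned sample size.** The inputs come from the Sample size section. For the error rates it states "Alpha was set at 0.05, and the beta was set at 0.20"; sidedness is not stated, so two-sided is assumed. The target is a 7-point difference. For the spread it states that "the standard deviation of the population outcome was 18". Allocation to the two arms is equal.

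n per group = 2 × (1.960 + 0.842)² × 18² / 7² ≈ 103.8, rounded up to 104.

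This matches the plan: "the necessary sample size was calculated to be 104 in each of the 2 groups". A one-sided test would need 82, so the two-sided reading is the right one. With 138 recruited and 32% lost in each arm, 138 × 0.68 = 93.8 per arm remain, which gives 75.9% power.

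**Step 2. Bias from unequal loss.** Let d_I and d_C be the drop-out proportions. Let G be the mean score of those retained minus the mean score of those lost, taken as equal in both arms. In each arm the completer mean exceeds the full-arm mean by d × G, so

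bias in (intervention − control) = G × (d_I − d_C).

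The document gives neither drop-out by arm nor G, so both are assumptions. d_C is held at the planned 32%, because extra effort in one arm is no reason for loss in the other to rise above plan. G = 9 points is half the SD (0.5 × 18).

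| d_I | G × (d_I − 0.32) | Share of 7 points | Power for 7 points |
|---|---|---|---|
| 32% | 0 | 0% | 75.9% |
| 25% | 9 × (−0.07) = −0.63 | 9% | 77.9% |
| 20% | 9 × (−0.12) = −1.08 | 15% | 79.1% |
| 15% | 9 × (−0.17) = −1.53 | 22% | 80.2% |
| 10% | 9 × (−0.22) = −1.98 | 28% | 81.1% |

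Over the same range of d_I from 25% to 10%, G = 5 gives 0.35 to 1.10 points (5% to 16%) and G = 18 gives 1.26 to 3.96 points (18% to 57%).

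The negative sign holds when those lost are worse off and the texts work: the bias then runs against the video. If those lost are better off, the sign reverses. Power rises slightly as more intervention participants stay, so the harm is bias and not loss of precision.

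**Step 3. Contact effect.** Suppose that the video does nothing but contact shifts the self-reported score by b points. With 93.8 per arm the standard error is 18 × √(2/93.8) ≈ 2.63. The two-sided rejection probability is Φ(b/2.63 − 1.96) + Φ(−b/2.63 − 1.96).

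| b (assumed) | Chance of a significant result |
|---|---|
| 0 | 5% |
| 1 | 6.7% |
| 2 | 11.9% |
| 3 | 20.8% |
| 3.5 | 26.5% |

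The document does not say how large b is, or that it differs from zero.

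**The case against.** The strongest reply is that contact belongs to delivery. The Introduction says that the feasibility study led to adjustments in follow-up after the video, and comparing a supported video with usual care is a legitimate pragmatic design. That stands for the link help. It does not cover texts whose stated purpose is retention, and it would make the tested intervention more than the video named in the aim.

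The document is also a condensed article, and its schedule figure is not available. Reminders for controls, and methods for missing data, may be set out elsewhere. This limits what can be said about consequences. It does not change the fact that the article assigns a named retention measure to one arm.

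A reader might infer stronger points that the document does not support:

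- **That differential drop-out is built in.** No drop-out by arm is given. Handling a link could add burden in the intervention arm, in which case support there might reduce an imbalance. Only a risk can be claimed.
- **That the arms differ by several personal contacts against none.** Three texts are stated, the number of calls is not, and the one-week check could be one of those calls. One contact in the Monitoring section is not limited by arm, although it is not a retention measure.
- **That the one-week check misses people whose link failed.** Read literally, it is aimed at those who have viewed the video. Its stated purpose is to check access, however, and the phone help in the Intervention section covers failed links. This is loose wording and not a gap.
- **That a positive result could not be credited to the video at all.** The texts and link help are a small co-intervention of unknown effect. They blur attribution but do not remove it.

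**Conclusion.** The point holds as a design weakness that is cheap to remove. A retention measure is stated for one arm only, in a trial with unblinded participants, a self-reported primary outcome and 32% expected loss. This creates a foreseeable risk of allocation-dependent drop-out and mixes contact with the effect under test.

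The size and direction of any bias are unknown. The range of about 0.6 to 2.0 points is an illustration that rests on four assumptions: control loss of 32%, intervention loss between 25% and 10%, a 9-point gap common to both arms, and a comparison of completers. The rejection probabilities likewise rest on assumed contact effects. What is certain is the one-sided assignment; the bias figures show only that the consequence need not be negligible against a 7-point target.

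**What to change.** - Send the retention texts to both arms, weekly for the first 3 weeks, with identical neutral content: thanks and a reminder of the 3-month visit, with no dietary advice.
- Keep technical help with the link as a separate component of the intervention arm.
- Describe the tested intervention as the video plus that link support, so that the aim and the eventual conclusion match what is delivered. Renaming alone would not be enough, because equal retention effort is still needed.

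The cost is three texts for each of 138 controls, 3 × 138 = 414 messages, from staff who already send them to the other arm. The requirement of 104 evaluable participants per group does not change. The small downside is that controls receive slightly more contact than usual care.

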### Measurements

The measurements will mainly focus on basic information, health-related quality of life, body composition measurements and readmission to hospital. The same externally trained data collector will carry out all measurements during the patients’ hospital stays and 3 months after discharge. We will register the number of readmissions within 3 months after discharge from the hospital. Figure 1 shows the schedule for enrolment, the intervention and the assessment of the trial according to the SPIRIT template.

**Fig. 1 Fig1:**
[figure not shown]
SPIRIT figure

### Demographic and clinical information collection

The patients’ demographic information, including name, age, email address, phone number, level of education and need for home care, will be collected at the baseline in the hospital. Information on LOS and the number of readmissions will be collected from hospital records 3 months after discharge. This trial will not involve the collection of biological specimens for storage.

### Primary outcome

#### Health-related quality of life

Health-related quality of life will be assessed using the 36-item Medical Outcomes Study Short Form Questionnaire (RAND 36). The RAND 36 is grouped into eight health concepts using multi-item subscales that are combined into two main scales summarising physical and mental health. The physical health component correlates mainly with the subscales of bodily pain, physical functioning and role limitations on physical scales [60]. The mental health component correlates mainly with the three subscales of social functioning, mental health and role limitations on emotional scales [60]. The two subscales of general health and vitality have noteworthy correlations with both the mental and physical health components [60]. The participants’ answers will then be analysed and given a score following the recommendations of the RAND Corporation [61].

### Secondary outcome

#### Body mass index

The participants will be weighed upon admission to the hospital. Their weight will be measured in the morning, when they are wearing light clothes without shoes and using the electronic Withings Body Cardio WBS04; their weight will be recorded to the nearest 0.1 kg. To be sure that only the Withings Body Cardio weight will be used in all weight measurements, the use of bed weights will be prohibited during this project. If participants cannot stand on the scale, weight data will not be collected. Height will be estimated based on forearm length, counting the ulna length between the point of the elbow and the midpoint of the prominent bone on the wrist. This value will be compared to the values in a standardised high conversion chart from RxKinetics [62] and recorded to the nearest 0.5 cm. BMI will then be calculated based on participants’ weight (kg) divided by the square of their height (m) [63]. Values < 24 kg/m^2^ will indicate malnutrition.

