**Method:**

This randomised controlled trial will occur at a regional hospital in Norway. Participants will be live-at-home adults aged 65 years and older. They will be recruited from three different surgical departments after a surgical procedure. Individuals with a body mass index below 24 and a home address in one of nine selected municipalities will be eligible for inclusion. Participants will be randomly assigned to either the intervention group or the control group. Those assigned to the intervention group will obtain access to a 6-min educational video 5 days after being discharged from the hospital. The control group will not obtain access to the video. The primary outcome will be health-related quality of life using the Norwegian Rand 36-Item Short Form Health Survey. Furthermore, we will measure body composition, number of readmissions and nutritional knowledge at inclusion and 3-month follow-up.

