Balancing cost-effectiveness and quality when providing care for older adults is challenging [16]. Person-centred care is often described as a model or philosophy of care that aims to acknowledge, involve and build upon the subjective experiences, needs, priorities, preferences and values of the person in need of care [16]. Person-centred care has been considered an appropriate approach to meet the challenges facing the healthcare system, but no consistent, agreed-upon parameters for providing such care exist [17]. A previous review found that person-centred care depends on [1] patient participation and involvement, [2] the patient–health professional relationship and [3] the care context [18].

The European Society for Clinical Nutrition and Metabolism (ESPEN) defines ‘malnutrition’ as the ‘deficiency, excess or imbalance of protein, energy and other nutrients, causing measurable adverse effects on tissues and function, and clinical outcome’ [19]. Although malnourished individuals can be over or undernourished, ‘malnutrition’ is often considered to be synonymous with ‘undernutrition’ [20]. The terms ‘undernutrition’ or ‘protein–energy malnutrition’ are further utilised to describe inadequate protein and energy intake or absorption [19]. Being at nutritional risk indicates that an individual is at risk of developing malnutrition or undernutrition. Disease-related malnutrition occurs due to diseases and disease states that entail the loss of body fat and muscle tissue [21]. Disease-related malnutrition is further connected to reduced dietary intake, increased nutrient loss, malabsorption or altered metabolic demands [20]. Older adults with a body mass index (BMI) lower than 24 are at nutritional risk [22]; therefore, it is recommended that older adults have a BMI between 24 and 29 [22].

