### Hypotheses

This study hypothesises that translating nutritional guideline recommendations regarding the intake of energy and protein using a digital medium for older adults aged 65 years and older will stimulate them to increase their intake of energy and protein in the recovery phase after discharge from the hospital following a surgical procedure. This will prevent loss of weight, loss of muscle mass and declines in health-related quality of life.

To verify the hypothesis, the following data will be collected: The participants in the inclusion group will be measured on their knowledge of highly recommended food choices, maintenance or increase of their BMI, mid-arm circumference (MAC), triceps skinfold thickness (TSF), mid-arm muscle circumference (MAMC), handgrip strength, knowledge of nutritional choices and health-related quality of life 3 months after discharge from hospital.

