### Participants and recruitment strategy

Surgical patients over 65 years of age will be eligible to participate in the study if they meet the following criteria:They are inpatients.Their home address is one of the municipalities affiliated with the selected hospital.They live at home and are due to return home after discharge directly from hospital or after a short-term training stay at a training centre before returning home.They can read and understand Norwegian.They have consent competence.They have a mobile phone or PC/tablet able to connect to the Internet.They have a body mass index < 24.

Following guidelines by Helsedirektoratet [54] and using NRS 2002 [55] for nutrient screening, the study will be based on the premise that all bedridden older adults undergo nutrition screening during their hospital stay and therefore have a known BMI. Patients receiving only liquid diets, such as tube feeding or intravenous nutritional support, and terminally ill patients will be excluded from the study.

The first author will have access to the department’s record system and will be responsible for informing and obtaining consent from eligible patients. The first author will enter the data into a spreadsheet and assign the participants to the intervention or control groups after the randomisation has been done. Furthermore, a trained external data collector who is not involved in the project will perform all the measurements.

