## Discussion

The combination of an increasing number of older adults and short hospitalisation times will result in an increased need for early rehabilitation after hospitalisation. To our knowledge, this study is the first to investigate the effectiveness of an educational video designed to improve patients’ knowledge to ensure they intake a sufficient amount of energy and protein at home following a surgical procedure and hospitalisation. The results will yield evidence on how educational videos can prevent disease-related malnutrition, preserve older adults’ functionality after a hospital stay and reduce healthcare costs. Furthermore, digital health solutions can help alleviate staff shortages.

To ensure that the study addresses its specified purpose and hypotheses, validated measurement tools will be used. An earlier systematic review and meta-analysis found that nutritional intake can improve physical performance outcomes (e.g. handgrip strength) in older adults who were already affected by specific medical conditions or by sarcopenia or frailty [66]. Maintaining internal validity can be challenging, as body composition measurements among older adults are difficult to record, and the interpretation of the data can be more problematic and prone to error [67]. The method used to measure body composition should be convenient and easy to implement. It can be difficult to measure the height of patients with fractures when using the method of having them stand up against a wall. Therefore, the participants’ heights will be estimated based on the length of their forearms because this is the most convenient method for the participants that can simultaneously ensure validity, in contrast to patients self-reporting their height.

Skinfold measurements are considered a valid method for assessing a person’s body fat [67]. However, such measurements can be challenging to perform, as the difference between adipose tissue and muscle is more difficult to palpate in older adults [67]. It can also be hard to measure bedridden patients. Therefore, we will enlist trained personnel in the performance of measurements.

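### BMI below 24 is both the entry criterion and the malnutrition cut-off, so the BMI category cannot show that malnutrition was prevented

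*Protocol article*

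**What the plan says.** The threshold of 24 appears in three roles in the protocol article.

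- **Entry.** The list under Participants and recruitment strategy includes "They have a body mass index < 24". The abstract agrees: "Individuals with a body mass index below 24 and a home address in one of nine selected municipalities will be eligible for inclusion".
- **Risk.** The Introduction states "Older adults with a body mass index (BMI) lower than 24 are at nutritional risk" and explains the term: "Being at nutritional risk indicates that an individual is at risk of developing malnutrition or undernutrition".
- **Outcome class.** The section on body mass index, under Secondary outcome, says that values below 24 kg/m² "will indicate malnutrition".

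Two other places set the context. The Hypotheses section treats BMI as a matter of direction of change: "maintenance or increase of their BMI". The Discussion presents the trial as being about prevention: "The results will yield evidence on how educational videos can prevent disease-related malnutrition".

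**The concern.** The Introduction separates being at risk from being malnourished, whereas the outcome section gives the at-risk value the malnutrition label. This is a conflict between stated definitions, not a detail that an analysis plan would settle.

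It also matters for what the outcome can show. To demonstrate prevention, an outcome needs participants who start outside the bad state and could enter it. Here the recruitment rule places everyone inside that state. If a BMI-based malnutrition frequency were reported, it would miss the deterioration that the video is meant to prevent, and a reader could take similar frequencies in the two arms as a finding about prevention.

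**Working it through.** The protocol gives no numerical target for the BMI category, so there is no planned figure to reproduce. The check is one of definitions, followed by simple arithmetic.

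**Step 1: status at entry.** Eligibility requires BMI < 24, and the malnourished class is BMI < 24. On the eligibility BMI, the proportion classed as malnourished is 100% in each arm. The number who could newly become malnourished is 0 in each arm, so no incidence can be compared.

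**Step 2: which changes register.** Take a participant who enters at BMI 23.

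- Falls to 20: below 24 before and after, so no change of class.
- Stays at 23: no change of class.
- Rises to 24 or above: leaves the class.

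The category treats the first two alike, although the trial exists to tell them apart.

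**Step 3: size of the movement that is seen and unseen.** Weight change in kg = change in BMI × height². Height is not given in the protocol. I assume 1.68 m, where 1.68² = 2.8224, and show a range of 1.60 m (2.56) to 1.75 m (3.0625).

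| Movement | 1.60 m | 1.68 m | 1.75 m | Changes class? |
|---|---|---|---|---|
| Gain, 23 to 24 | 2.6 kg | 2.8 kg | 3.1 kg | Yes |
| Gain, 22 to 24 | 5.1 kg | 5.6 kg | 6.1 kg | Yes |
| Gain, 20 to 24 | 10.2 kg | 11.3 kg | 12.3 kg | Yes |
| Loss, 23 to 20 | 7.7 kg | 8.5 kg | 9.2 kg | No |

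A loss of about 8.5 kg is invisible to the category. The gain needed to register depends mainly on how close to 24 the participant happened to start.

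**Step 4: what is left.** Analysed as a number, the fall from 23 to 20 counts as −3 and contributes to the difference between arms. Mid-arm circumference and mid-arm muscle circumference have cut-offs of their own that are not entry criteria.

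**The case against.** The strongest reply is that no BMI-based malnutrition rate is clearly planned. The Data analysis section assigns means, standard deviations, confidence limits and parametric tests to interval and ratio data, which BMI is. Its remark on numbers and frequencies is general and does not name BMI. The Hypotheses section frames BMI as maintained or increased, which remains meaningful when everyone starts below 24. The main aim is health-related quality of life, and the prevention sentence in the Discussion is not tied to this cut-off. All of this stands, and it limits the point to one sentence on a secondary measure. It does not remove the point, because that sentence is written as a classification rule under an outcome and contradicts the Introduction.

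A reader might infer two stronger things that the documents do not support.

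- **That everyone is malnourished on the trial's own baseline measurement and nobody could ever enter the class.** This is exact only for the BMI used for eligibility, which comes from ward screening. Trial BMI uses a specified scale and a height estimated from the forearm. The protocol does not say which scale or height method screening uses. If the two differ, some participants could start at or above 24 on trial BMI and later fall below it.
- **That both arms would show spurious recovery through regression to the mean.** That would require comparing screening BMI with follow-up trial BMI, and the protocol does not plan this. One trained collector takes the measurements in hospital and at 3 months, with the same scale and height method, so selection on screening error affects both trial measurements alike. Any percentage for such crossings would rest on assumed measurement errors.

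**Conclusion.** The point holds as a minor one. One threshold serves as entry criterion, marker of risk and definition of malnutrition, and the last two conflict with each other. By the eligibility BMI, 100% of participants are in the class at entry, none can newly enter it, and further loss leaves the class unchanged. The category therefore cannot support a statement that malnutrition was prevented; at most it could show a return to 24 or above.

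This conclusion follows from the definitions and needs no assumption about measurement error. Only the weights in kilograms depend on an assumed height. The randomised comparison of continuous BMI remains valid.

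**What to change.** Reconcile the Introduction, the recruitment criteria and the section on body mass index. Either delete the sentence that equates values below 24 kg/m² with malnutrition, or relabel the category as at nutritional risk and use it for description only.

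State that 3-month BMI is analysed as a continuous outcome, with the arms compared after adjustment for baseline BMI as measured by the trial, for example by analysis of covariance. This improves on the unadjusted t-test and analysis of variance that the Data analysis section names, and the baseline value is already collected. Participants who cannot stand on the scale have no trial weight, so the analysis should say how a missing baseline BMI is handled.

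The cost is one sentence deleted or reworded and one line added on the analysis. No extra data or participants are needed. The trial gives up only a BMI-based malnutrition frequency that says nothing about prevention.
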